#### **4 Implementation strategy and procedure**

After selecting the hospital and allocation in either experimental or control, the meeting with the hospitals will be organised. One blinded research assistant who will be different from the one who has selected the hospitals will be trained to audit medical records of all discharged patients until a maximum of 100 records in each hospital have been audited. This person will be trained on basic ICF framework and needed information from the patients' folders, and how the records will be accessed and filled as well as the selection criteria. Research assistants will also collect data from health care professionals. The measurements will be taken at baseline (one month before training) and after training. Before training, the following measurement will be performed:

- Monitoring knowledge, attitudes and behaviour of the health care professionals towards interprofessional practice (Appendix v), holistic care (Appendix vii) and the impact of functioning and environmental context on patient well-being and quality of life (Appendix viii).
- Auditing the quality of patient's records, referral and discharge note (Appendix vi)

The researcher will again train another different research assistant who will help during training. One week after, the researcher and research assistant will plan the intervention. The training procedure will be based on that used during the feasibility study, but will be adapted as needed according to the experience from the feasibility study. After training the researcher and the trained health care professionals will hold a consensus meeting regarding implementation and how they can start introducing new forms to be used with the existing records. The control hospitals would receive no training during this time, but they will be given some basic introduction on ICF theoretical. For Experimental hospitals, two months follow-up will be done after training in order to check if there are some challenges and questions during practice. Again, the comparator hospitals will receive no follow up. Three time data collection also will be done at 2nd month, 4th month, and 6th month after training will be performed in both experimental and control.

After training, the following measurement will also be performed:

- Determining the satisfaction of health care professionals with ICF training and the method of implementation (Example: Appendix iv).

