| 8. Marital status                                                                                                              |  |  |  |
| 9. Medical aid/No medical aid                                                                                                  |  |  |  |
| 10. Patient occupation                                                                                                         |  |  |  |
| 11. Level of education                                                                                                         |  |  |  |
| 12. Admit date                                                                                                                 |  |  |  |
| 13. Discharge date                                                                                                             |  |  |  |
| C. Comprehensive assessment                                                                                             |                          |                          |                          |
| 14. Health condition and diagnosis                                                                                             |  |  |  |
| 15. Symptoms                                                                                                                   |  |  |  |
| 16. Assessment of impairment                                                                                                   |  |  |  |
| 17. Impact of condition on functioning (Use ICF checklist. If yes, put the number of functioning addressed in the box).        |      |  |  |

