| 18. Impact of environmental factors (Use ICF Checklist. If yes, put the number of Environmental factors addressed in the box). |      |  |  |
| D. Holistic intervention                                                                                                |                          |                          |                          |
| 19. Health condition managed in context                                                                                        |  |  |  |
| 20. Personal factors including mental and spiritual needs                                                                      |  |  |  |
| 21. Impairment addressed                                                                                                       |  |  |  |
| 22. Functioning addressed                                                                                                      |  |  |  |

|                                                                                                 |                          |                          |                          |
|-------------------------------------------------------------------------------------------------|--------------------------|--------------------------|--------------------------|
| 23. Environmental factors addressed                                                             |  |  |  |
| E. Continuum of care and discharge                                                       |                          |                          |                          |
| 24. Preventive measures of recurrence of health condition or complications related to condition |  |  |  |
| 25. Referral to other services                                                                  |  |  |  |

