## 5.7 Appendix vii: Interprofessional care framework for continuous interprofessional care (based on ICF)

|                                  |                        |                   |
|----------------------------------|------------------------|-------------------|
| Patient sticker           | Diagnosis:      |                   |
|                                  | Admission date: |                   |
| Impairment                | By who          | Management |
|                                  |                        |                   |
|                                  |                        |                   |
| Activity limitation       | By who          | Management |
|                                  |                        |                   |
|                                  |                        |                   |
| Participation restriction | By who          | Management |
|                                  |                        |                   |
|                                  |                        |                   |
| Personal factors          | By who          | Management |
| Positive                  |                        |                   |
|                                  |                        |                   |
|                                  |                        |                   |
| Negative                  |                        |                   |
|                                  |                        |                   |
|                                  |                        |                   |
| Environmental factors     | By who          | Management |
| Facilitator               |                        |                   |
|                                  |                        |                   |
|                                  |                        |                   |
| Barrier                   |                        |                   |
|                                  |                        |                   |
|                                  |                        |                   |

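### The record audit is called blinded, but new forms are planned only for experimental hospitals' folders and no masking is described, so the post-training audits cannot be assumed blinded

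*Combined protocol and SAP*

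**What the plan says.** Section 4 (Implementation strategy and procedure) gives the audit to a single person: "One blinded research assistant who will be different from the one who has selected the hospitals will be trained to audit medical records". It does not say what this person is blinded to or how blinding is kept. The auditor works from the folders: "This person will be trained on basic ICF framework and needed information from the patients' folders".

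After training, the researcher and the trained staff meet to agree "how they can start introducing new forms to be used with the existing records". For the other arm: "The control hospitals would receive no training during this time, but they will be given some basic introduction on ICF theoretical". No forms and no follow-up visit are described for the comparator hospitals.

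The only ICF-based form for a patient record in the appendices is Appendix vii, "Interprofessional care framework for continuous interprofessional care (based on ICF". The audit tool is Appendix v, with items such as "16. Assessment of impairment" and "17. Impact of condition on functioning (Use ICF checklist. If yes, put the number of functioning addressed in the box".

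Section 3.2.2.2 makes the record score part of the primary outcome, together with better interprofessional practice. Section 3.2.2.3 sets 100 records per hospital at baseline and at two, four and six months, and lists by name which hospitals are in which arm.

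**The concern.** If an ICF form appears in experimental folders only, an auditor trained in the ICF can recognise the arm from the folder. Several audit items call for judgement, such as whether functioning was addressed or the condition was managed in context. An auditor who knows the arm may be more generous to trained hospitals, which would favour the intervention.

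The second issue is meaning. The form asks for much of what the audit counts. A higher score could show that staff completed a new sheet, while the trial also wants to conclude that interprofessional practice improved. The multi-level regression in section 4.1 allows for clustering in the variance. It does not remove a systematic difference in how the two arms are scored.

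**Working it through.** **1. How many audits are exposed.** Inputs are from sections 3.2.2.2 and 3.2.2.3.
- Hospitals: 20% × 40 = 8. Records per occasion: 8 × 100 = 800, which reproduces the plan's figure.
- All four occasions: 4 × 800 = 3,200. After training: 3 × 800 = 2,400.
- Experimental hospitals after training: 4 × 100 × 3 = 1,200, the most that could contain the form. The plan gives no uptake or start date, so the actual number may be lower.

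**2. Whether blinding can hold.** Set side by side, section 4 has an auditor called blinded, folders as the material, new forms planned by trained staff, and no forms mentioned for the comparator. Nothing describes removing or covering forms, hiding the hospital, or a second rater in the main trial. The two-rater ICC in section 3.1.5 belongs to the feasibility study. Baseline precedes training, so no form is in the folders then.

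**3. Overlap of the likely form with the audit.** Appendix v has 30 items. Sections C to F, which cover content rather than consent and demographics, are items 14 to 30, so 17 items.

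| Appendix vii heading | Appendix v items on the same concept |
|---|---|
| Impairment | 16, 21 |
| Activity limitation; Participation restriction | 17, 22 |
| Personal factors | 20 |
| Environmental factors | 18, 23 |
| Diagnosis | 14 |

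That is 7 of 17 (41%) without Diagnosis and 8 of 17 (47%) with it. Items 19, 28, 29 and 30 could plausibly be met from the columns for the responsible person and the management, giving at most 12 of 17 (71%). Items 15 and 24 to 27 have no matching heading.

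The overlap could weigh more, depending on the scoring. Items 17 and 18 take a count from Appendix vi, which lists 48 activity and participation codes and 32 environmental codes. If those counts were added into the total (an assumption), the maximum for sections C to F would be 15 + 48 + 32 = 95. The eight matched items would hold 6 + 80 = 86 of these points (91%).

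**4. Why no size can be given.** The documents state no scoring rule, SD, ICC, power or detectable difference; section 3.2.2.2 defers the calculation. The following is illustration only.
- One extra yes per experimental record, equal weights: 1/17 = 5.9 percentage points on sections C to F, or 1/30 = 3.3 on the whole checklist.
- With an assumed SD of 10 to 20 points, that is 0.59 to 0.29 SD on 17 items, or 0.33 to 0.17 SD on 30.
- Difference detectable with 4 against 4 hospitals, 100 records each, one time point, 80% power, two-sided 5%, t on 6 df. The standard error in SD units is √(2 × (1 + 99 × ICC)/400). Solving with the non-central t gives 0.34 SD at ICC 0.01, 0.41 at 0.02, 0.58 at 0.05 and 0.79 at 0.10.

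The illustrative shift can be below or above the detectable difference, depending on values that the plan does not supply.

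**The case against.** Four points on the other side carry weight.

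- **The form is inferred.** No text names Appendix vii as the new form. Section 4 cites that number for a holistic-care measure and section 4.2.1 for the superintendent letter, and the intervention may change after the feasibility study. This stands as a caveat. The unmasking point does not depend on it, because any ICF form filed only in experimental folders would show the arm.
- **A heading is not an entry.** A reader might infer that the printed headings themselves earn the score, or that blinding certainly ends with the first post-training folder. The documents support neither. Items 17 and 18 need specific factors to count, and no uptake date is fixed.
- **Prompted recording is partly the intended effect.** Section 1.4.2 treats changed recording as the sign of improved practice, Appendix i ties behaviour to patient records, and record completeness is in the primary outcome. This stands for claims about documentation. It does not settle claims about interprofessional practice, which the primary outcome also names.
- **The feasibility study covers some of this.** It is to examine whether records reflect actual practice and to reach 80% rater agreement. That helps with consistency. However, it takes place in one hospital with no comparison arm, so it cannot show how an auditor who knows the arm will score.

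A reader might also infer that the bias is about as large as the difference the trial can detect. On the illustration of 0.39 SD (5.9 points, SD 15), that holds only for an ICC near 0.02, and the plan gives neither the SD nor the ICC.

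**Conclusion.** The concern holds in limited form. As written, the plan cannot keep the audit blinded after training: the auditor reads the folders, only experimental hospitals are to add forms, and no masking is described. The 2-, 4- and 6-month audits should not be assumed blinded, and any detection bias would favour the intervention. Seven or eight of 17 content items share a concept with the likely form, so part of a higher score may reflect form completion. This rests on two inferences: that Appendix vii or a similar form is what is introduced, and that comparator folders receive none. The direction of the bias is clear, but its size cannot be derived from the documents.

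**What to change.** Settle the following in section 4 and the audit manual before the first post-training audit.

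1. Describe the audit as blinded at baseline only, and as unblinded to arm at 2, 4 and 6 months, unless masked extracts are used. Such extracts would need to hide the hospital as well as the form layout, since section 3.2.2.3 names each hospital's arm.
2. Score an item as yes only on a patient-specific entry, never on a printed heading.
3. Have the same auditor record, for each yes, whether the source is the routine notes or the new form.
4. Report the full score as the documentation outcome, with a prespecified sensitivity score that excludes form-only entries.
5. Do not claim changed interprofessional practice (items 27 to 30, section F of Appendix v) if the difference appears only in form-derived entries.

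The cost is a little more time per folder; no extra rater is needed. Recording the source addresses form completion. It does not restore blinding, which is why the label must change. The sensitivity score may understate real change if entries move from the notes to the form, including genuine evidence for items 28 to 30. Both scores should therefore be reported.

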#### ***3.2.2.2 Sample size calculation***

It is anticipated that a 20% (8) sample of 40 district hospitals will allow the outcomes to be generalised to the other hospitals. In their study, Zegers et al. (2007) reviewing patients records in Dutch hospital, a random sample of 20% of the hospitals was selected and the results were

generalized. At each hospital all the relevant health professionals will be included in the training so the sample will be one of convenience. The primary outcome of this study will be the improved interprofessional practice within the district hospitals and comprehensiveness of the patients' records demonstrated by the scores. A sample size calculation will be done once the needed tools have been finalised and the mean and standard deviation calculated during a feasibility study. However as multi-level regression analysis will be done to account for the effect of clustering, a sample of 800 patients records (100 from each hospital) should allow for the analysis of at least 80 variables. This is a large number but, as it is anticipated that the effect size will be small due to the presence of so many confounding variables, a large sample size will be required to prevent a Type II error from occurring.

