### ***3.2.2.3 Recruitment and sampling method***

#### **District hospitals**

Cluster random sampling will be used by a blinded person to select the district hospitals within 40 districts of four provinces. It is anticipated that eight district hospitals will participate in this study. The sample will include Gahini hospital, Kiziguro hospital, Nemba hospital, Rutongo hospital, Remera Rukoma hospital, Nyanza hospital, Byumba hospital, and Ruhango hospital. The same individual will randomly allocate four hospitals on the experimental arm and other four hospitals on the comparator arm. The experimental hospitals will include: Gahini hospital, Nemba hospital, Rutongo hospital, and Remera Rukoma hospital. The comparator hospital will be composed of Kiziguro hospital, Ruhango hospital, Byumba hospital, and Nyanza hospital.

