#### **Medical records**

A stratified sampling method will also be used to select the patients' medical records that will meet the inclusion criteria to be involved in the study. It is anticipated to have a maximum of 100 patients' records per hospital. In each hospital, 100 patients' records will be audited at each occasion: baseline, two months, four months, and six months after intervention. Only the records of

discharged patients will be audited as well the records of discharged patients during two months of data collection.

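### Audited records are chosen by two incompatible rules, their total is undefined (800 or 3,200), and post-training records need not come from patients admitted after training

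*Combined protocol and SAP*

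**What the plan says.** On the number of records:

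- Section 3.2.2.2 says that "a sample of 800 patients records (100 from each hospital) should allow for the analysis of at least 80 variables". It gives no time point.
- Section 3.2.2.3 (Medical records) says "It is anticipated to have a maximum of 100 patients' records per hospital", again with no time point. Its next sentence sets 100 for each hospital and says that these "records will be audited at each occasion: baseline, two months, four months, and six months after intervention".
- Section 4 repeats a ceiling of 100 per hospital without naming an occasion.

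On how they are chosen:

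- Section 3.2.2.3 states "A stratified sampling method will also be used to select" the eligible records. It does not name the strata, the allocation or the list to sample from.
- Section 4 describes an assistant who "will be trained to audit medical records of all discharged patients until a maximum of 100 records in each hospital have been audited".

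On timing, section 3.2.2.3 mentions two months of data collection, and section 4 places follow-up at months 2, 4 and 6 after training. Neither says when a window opens or closes. Section 3.2.2.1 requires a stay of at least five days in one of three wards and a completed discharge. It sets no condition on the admission date relative to training.

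**The concern.** Comprehensiveness of the patient records is part of the primary outcome (section 3.2.2.2), so the way records are selected acts directly on the main comparison. A stratified draw and an audit of every discharge up to a ceiling give different samples. Two teams working from this plan would pull different folders.

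Under the section 4 rule, nothing fixes how many records come from each ward or how much of the window they cover. Both follow throughput, which can differ between hospitals and between occasions within a hospital. The score is not neutral to ward. Appendix v scores marital status, occupation and education (items 8, 10 and 11). The ICF checklist in Appendix vi, which feeds counts into items 17 and 18, includes driving (d475), intimate relationships (d770) and remunerative employment (d850). These will often not apply to a child. Appendix v has a not-applicable column; Appendix vi offers only yes or no. A shift in ward mix can therefore move the score with no change in practice, and with four hospitals per arm such shifts need not average out.

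Separately, a record may have been largely written before any staff were trained and still count as post-training.

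**Working it through.** **1. The plan's own figure.** 20% of 40 hospitals is 0.20 x 40 = 8, and 8 x 100 = 800, so 800 reproduces. It implies 800 / 80 = 10 records per variable.

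**2. The other total.** 8 hospitals x 100 records x 4 occasions = 3,200, of which 8 x 100 x 3 = 2,400 fall after training. The ratio 3,200 / 800 is 4. If 800 were the total over all occasions, each hospital would supply 800 / (8 x 4) = 25 records per occasion.

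**3. How fast a quota of 100 fills.** The only volume figure in the documents is the average of 182 beds (section 3.2.2). Everything else here is assumed: 30-75% of beds hold eligible patients, occupancy is 50-90%, mean stay is 7-14 days, and two months is 60 days.

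Eligible discharges per day = beds x share x occupancy / stay.

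- Slowest: 182 x 0.30 x 0.50 / 14 = 1.95 a day; 100 / 1.95 = 51 days; 117 in 60 days.
- Fastest: 182 x 0.75 x 0.90 / 7 = 17.55 a day; 100 / 17.55 = 6 days; 1,053 in 60 days.
- A narrower set (share 50-70%, occupancy 70-90%) gives 4.55 to 16.4 a day, so 22 down to 6 days.

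Over 27 combinations (share 30/50/75%, occupancy 50/70/90%, stay 7/10/14 days), none yields fewer than 100 in the window with full access to records. After training, access needs individual consent (section 4.2). At an assumed 50% consent the yield is 59 to 527, and 4 of the 27 fall below 100.

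**4. Ward mix when all discharges are taken.** With equal beds and equal occupancy, a ward's share is proportional to 1 / stay. Equal stays give about 33 records each. Assumed mean stays of 14, 8 and 6 days give weights 0.0714, 0.1250 and 0.1667 (sum 0.3631), hence about 20, 34 and 46 records.

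**5. Does the total drive power?** The plan gives no ICC or SD, so ICC is assumed. For 4 v 4 hospitals with m records each, the standard error in SD units is the square root of 2 x [1 + (m - 1) x ICC] / (4m). The detectable difference is taken from a t test on 6 df at 80% power and two-sided 5%.

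| ICC | m = 100 | m = 400 |
|---|---|---|
| 0.01 | 0.34 | 0.27 |
| 0.05 | 0.58 | 0.55 |
| 0.10 | 0.79 | 0.76 |
| 0.20 | 1.09 | 1.07 |

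From an ICC of 0.05 upwards, the number of hospitals limits power far more than the number of records.

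**6. Admission before training.** With a minimum stay of five days, an eligible patient discharged less than five days after training must have been admitted before it. This needs no assumption about mean stay. Whether such patients enter the first post-training sample depends on when that window opens. If it covers the two months ending at month 2, it opens at training and they do. If it begins at month 2, they do not. The plan does not say which applies.

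**The case against.** The case for the plan is reasonable in several places.

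- Section 3.2.2.2 does not call 800 a grand total. Read as per occasion, it agrees with section 3.2.2.3, so the fault is a missing qualifier and not an arithmetic error. That stands, but no section supplies the qualifier, and the ceiling of 100 appears untimed in three places.
- The section 4 sentence describes an auditor's training, and the next sentence adds that selection criteria will be taught. Auditing up to a ceiling could be run within strata. It could, but the plan does not say so and names no strata.
- Section 2.1 describes district hospitals outside Kigali as similar in patients and services. Section 4.1 compares diagnoses between groups, plans multilevel regression and allows diagnosis subgroups. These help, but they examine case mix after collection. They do not fix ward mix, and ward is not named as a covariate.
- Consent to record access is sought on admission or during the stay. This limits pre-training admissions without excluding them.

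A reader might also infer more than the documents support:

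- *That samples will be short.* The ceiling sets no minimum, but in the calculation above the quota fills in every scenario with full access. A shortfall appears only where volume is low and consent is assumed to be 50%. What the rule may shorten is calendar coverage.
- *That the ceiling of 100 is used up at baseline.* Sections 3.2.2.3 and 4 both schedule audits after training.
- *That the share admitted before training can be estimated as stay divided by days to reach 100.* Stay cancels, leaving occupied beds / 100. On the narrower inputs that is 63.7 / 100 to 114.7 / 100, or 64% to 115%, which is impossible at the top. The documents support no figure for this share.

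**Conclusion.** The point holds as a conflict between selection rules, an undefined total and a missing admission-date condition.

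The two selection rules are incompatible as written, and neither can be carried out without further decisions. The total differs by a factor of four unless 800 is declared to be per occasion. That matters more for the workload of the single auditor described in section 4, and for the stated basis of 80 variables, than for power.

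Uneven ward mix and restriction to the first weeks of a window are risks, not demonstrated outcomes. The documents give no ward volumes, occupancy, length of stay, consent rate or scores by ward. The 6 to 51 days and the 20/34/46 split rest on assumed values. That the ward mix is left unfixed, and that some items apply differently by ward, rests on the documents alone.

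The lack of an admission-date condition is also certain. Its effect, a diluted first post-training comparison, is conditional on that window opening at training.

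This should be settled before auditing starts, because an unplanned ward mix or an early-discharge sample cannot be fully repaired in analysis.

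**What to change.** - State one number in sections 3.2.2.2, 3.2.2.3 and 4: 100 records per hospital per occasion, 800 per occasion, 3,200 in all.
- Give opening and closing dates for each audit window, including the first after training.
- For each window, list all eligible discharges by ward (after training, those with consent). Draw a random sample stratified by ward, with the same allocation in every hospital and at every occasion. Equal thirds are one option; a common allocation reflecting the usual inpatient mix is another. If a ward cannot fill its stratum, top up at random from the other wards and report it.
- Remove the fill-to-100 wording from section 4.
- Include ward as a covariate in the multilevel model of section 4.1.
- For post-training occasions, include only patients admitted after the hospital's training date, and apply a matching calendar date in comparator hospitals. Appendix v items 12 and 13 already cover admission and discharge dates.

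The cost is protocol wording and a discharge list per ward for each window. Small wards may not fill their stratum, and a first window that opens at training would lose its earliest discharges.
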